## 6.5 **Clinical management and referral**.

All children with a positive RDT will be treated on site with the nationally recommended age-specific drug dosing regimen by a qualified nurse. Children identified as severely anemic (hemoglobin levels < 5 g/dL) will be referred to the nearest health facility for treatment according to national guidelines

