### 5.3.5 Clinical management

Respondents who are tested with an RDT and test positive for malaria shall be offered treatment for malaria in their homes. Respondents with a positive RDT and no evidence of severe malaria will be treated with artemether-lumefantrine, the standard national regimen. Respondents with a positive RDT and evidence of danger signs of severe disease will be referred to the nearest health facility for further evaluation and treatment. Respondents with a hemoglobin level of < 5.0 g/dL will be referred to the nearest health facility for further evaluation and transfusion. Any respondent with other concerning clinical symptoms will also be referred to an appropriate health care facility at the discretion of the study personnel.

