## 7.3. Rapid diagnostic tests

Using the same fingerprick made for anemia testing, a drop of blood will be tested immediately using the Paracheck rapid diagnostic test, which tests for *Plasmodium falciparum.* The test includes a loop applicator that comes in a sterile packet. A few microlitres of blood is captured on the applicator and placed on the well of the device. Results are available in 15 minutes. The results will be provided to the respondent in oral and written form and will be recorded on the Household Questionnaire. Those who test positive for malaria will be provided a full course of treatment for malaria according to the national standard malaria treatment guideline in Uganda. They will also be told to go to the nearest health facility immediately if their illness worsens.

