## 10.4 Potential benefits to participants

Several biological tests will be conducted in the field and results returned to the respondents and where feasible treatment, care or follow-up will be provided. Test results for anemia (indicating whether the child has non-severe anemia or severe anemia and test results for malaria with Rapid Diagnostic Tests will be given in the field. Those with severe anemia or severe malaria will be referred for medical treatment. Respondents testing positive for malaria with Rapid Diagnostic Testswill be offered a free full-course treatment with the recommended antimalarials.

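### The school procedure in section 6.5 does not carry out the referral for severe malaria that section 10.4 states for participants generally

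*Protocol*

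**What the plan says.** Four sections of the protocol deal with what happens after a positive RDT.

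- **Section 6.5 (schools).** "All children with a positive RDT will be treated on site", by a qualified nurse and under the national regimen. The next sentence gives the only referral in the section: "Children identified as severely anemic (hemoglobin levels < 5 g/dL) will be referred to the nearest health facility". Severe malaria, danger signs and other worrying symptoms are not mentioned.
- **Section 10.4 (potential benefits to participants).** "Those with severe anemia or severe malaria will be referred for medical treatment". It also says that those who test positive are offered a free course of treatment. Nothing in it restricts either statement to one survey.
- **Section 7.3 (RDTs, laboratory chapter).** "Those who test positive for malaria will be provided a full course of treatment for malaria". They are also told to go to a facility at once if they get worse. Nothing is said about a person who is already severely ill when tested.
- **Section 5.3.5 (community survey only).** RDT-positive respondents are divided: "Respondents with a positive RDT and no evidence of severe malaria will be treated with artemether-lumefantrine", whereas "Respondents with a positive RDT and evidence of danger signs of severe disease will be referred to the nearest health facility". It adds a discretionary clause: "Any respondent with other concerning clinical symptoms will also be referred to an appropriate health care facility".

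**The concern.** Section 6.5 is headed as the school survey's management and referral section, so a school team would look there for its referral rules. It carries through one half of what 10.4 states (severe anemia) and leaves out the other half (severe malaria). A team that follows 6.5 to the letter would therefore not make a referral that the ethics chapter describes.

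Participant safety is at stake, not inference. The children concerned may be the most ill of those seen in the school survey, and an ethics committee reading 10.4 would expect something that the school procedure does not state.

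**Working it through.** The plan states no figure on this point and none needs computing. The check is to follow each kind of RDT-positive schoolchild through the sections that could apply. The community rule is in the last column for comparison only.

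| RDT-positive child | 6.5 (schools) | 10.4 (general) | 6.5 and 10.4 agree? | 5.3.5 (community, context only) |
| --- | --- | --- | --- | --- |
| No severe signs, Hb 5 g/dL or more | Treated on site | Treatment offered | Yes | Treated at home |
| No severe signs, Hb below 5 g/dL | Treated on site and referred | Treatment offered and referred | Yes | Treated at home and referred |
| Severe signs, Hb below 5 g/dL | Treated on site and referred (because of Hb) | Treatment offered and referred | Yes, though 6.5 refers for anemia only | Referred |
| Severe signs, Hb 5 g/dL or more | Treated on site; no referral stated | Treatment offered and referred | **No** | Referred |

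1. The mismatch is confined to the last row. In the third row the child is referred under 6.5, but only because the hemoglobin criterion happens to be met.

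2. Section 7.3 does not repair the last row. Its advice depends on later deterioration, so it does not cover a child who already has severe signs at the assessment. The general encouragement in section 7.1 to seek care if ill after the survey likewise looks forward.

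3. Section 6.4 lists the school assessments: basic socio-demographic data, temperature, RDT, smears, filter paper and hemoglobin. It mentions no check for danger signs, so it does not supply the missing step either.

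4. Nothing shows the difference between the surveys to be deliberate. Both examine children aged 6 to 14 in the same sub-counties, and no reason is given for handling them differently.

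**The case against.** **Treating and referring are compatible.** This stands. Section 6.5 does not forbid referral or call its hemoglobin trigger exclusive, and a child with a positive RDT and hemoglobin below 5 g/dL receives both under its own terms. A team could follow 6.5 and 10.4 together. The fault is best described as a severe-malaria branch missing from 6.5, not as two orders that cannot both be obeyed.

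**Section 5.3.5 does not bind school staff.** This stands too. A reader might set 6.5 against 5.3.5 and infer that school teams hold contradictory instructions. The document does not support that: 5.3.5 belongs to the community chapter. It shows only that the protocol elsewhere treats severity as a point of division.

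**Section 10.4 describes benefits; it is not a procedure.** True, and its text speaks of respondents, a word that chapter 6 does not use for pupils. But its heading refers to participants, it sits in the ethics chapter for the whole study, and no other section states a severe-malaria rule for schools. If 10.4 is read as excluding pupils, the protocol says nothing about severe malaria in schoolchildren, and the gap in 6.5 remains.

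**A qualified nurse would act sensibly, and national guidance may cover the case.** Possibly. But 6.5 says all, it has no discretionary clause like that in 5.3.5, and the content of the national guidance is not in the protocol.

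Two further inferences should be resisted. One is that families are told something different from what is done. What parents are told is in the school consent form (appendix 6), which is not shown. The other is a count of 3,600: 3 schools × 100 children × 3 sites × 4 rounds. That is every enrolled school assessment over the minimum two years. It is not the number of RDT-positive children with severe signs, and it says nothing about how many are affected.

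**Conclusion.** The point holds as a mismatch between sections. For an RDT-positive schoolchild with signs of severe malaria and hemoglobin of 5 g/dL or more, 6.5 as written does not deliver the referral stated in 10.4, and 7.3 does not supply it.

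The conclusion assumes that 10.4 covers both surveys, which its heading and place in the protocol support, and that a school team works from 6.5 as written.

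The number of children affected cannot be derived from the protocol. It is probably small, since these are pupils attending school on the survey day, but the consequence for any one of them could be serious. Prevalence estimates, the comparison of methods and the power statements are untouched. The text should be corrected because the matter concerns safety and the correction is cheap.

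**What to change.** Reconcile section 6.5 with section 10.4 so that the protocol states one consistent procedure for RDT-positive schoolchildren with and without signs of severe disease. Check 7.3 and 5.3.5 in the same pass. If the two surveys are meant to differ, say so and give the reason. The investigators must decide the content of the rule; this review proposes none. When the wording is settled, the school consent form should be read against it.

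The cost is one or two sentences of protocol text and, under section 10.1, review by the ethics boards as an amendment if the protocol is already approved. Sample size, data collection and analysis do not change.

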## 6.6 GPS data collection.

Households of a subsample (20%) of the selected children will be mapped using hand-held GPS receivers. These households will be randomly selected from the list of surveyed children. The study team will escort the selected children home; verbal consent will be sought from an adult respondent found at home and GPS readings will be taken from the door of the household, if possible, or from a point that is most representative of the household. At each household, a reading will be taken every five seconds for 2 minutes, and the average values from these readings will be recorded (Easting, Northing, and Altitude) in UTM units. The GPS data collected will be used to estimate the geographical distribution of the students attending the school.

# 7.0 LABORATORY TESTING

## 7.1. Microscopy

Thick and thin blood smears will be prepared in the field for microscopy. New glass slides, frosted at one end, will be used to make the malaria blood smears. Before making the smears, the technician will place a barcode label on the under-side of the glass slides at the frosted end linked to the household questionnaire. At the end of each day, the thin smears will be immersed in absolute methanol for a few seconds in order to prevent auto-fixation of the blood cells. Slides will be kept at the field site protected from excessive heat and light for no longer than 2 weeks. The slides will be kept in a drying box with desiccant and stored in the coolest place possible. The desiccant shall be checked daily to ensure that it is working properly. The blood slides for malaria will be periodically transported to the UMSP Molecular Research Laboratory in Mulago. All specimens will be accompanied by a list of samples generated from the questionnaire and linked to the bar codes of the specimens.

The blood slides for malaria will be read at the UMSP Molecular Research Laboratory in Mulago. Thick and thin blood smears will be stained with 2 percent Giemsa for 30 minutes. Thick blood smears will be evaluated for the presence of parasitemia (asexual forms only) and gametocytes. Parasite and gametocyte densities will be calculated from thick blood smears by counting the number of asexual parasites and gametocytes, respectively, per 200 leukocytes (or per 500, if the count is less than 10 parasites or gametocytes per 200 leukocytes), assuming a leukocyte count of 8,000/l. A thick blood smear will be considered negative when the examination of X 100 high power fields does not reveal asexual parasites or gametocytes. Thin blood smears will be evaluated to determine parasite species. Thin smears will be read only when the thick smear reading is positive. For quality control, all slides will be read by a second microscopist and a third reviewer will settle any discrepant readings.

Results of blood slides will not be returned to participants. RDT results, however, will be provided to participants on the spot and treatment offered if RDT results are positive, and the participants will be told to seek care at the health facility if illness worsens. It is possible that for some cases, the RDT will be negative, but microscopy will be positive. The most likely reason for an RDT to be negative when microscopy is positive comes from those people with low levels of parasitemia below the level of detection for RDTs but not below the level for microscopy. The risk of developing symptomatic or severe illness is very low from a presumably low parasitemia in an RDT-negative asymptomatic individual. It is worth noting that RDTs are used nationally at the point of care in health facilities, and confirmatory microscopy is usually not performed. Regardless of the RDT results, all participants will be encouraged to seek treatment at health facilities should they become ill following the survey.

## 7.2. Measurement of hemoglobin

Hemoglobin analysis will be carried out on site using a drop of blood collected from a finger-stick (or heel stick). The test will be conducted using a battery-operated portable HemoCue analyzer which produces a result within one minute. Results will be returned verbally and in written form and those who have severe anemia requiring treatment (under 5 g/dl) will be provided with information on local health facilities where treatment can be obtained and they will be urged to go to these health facilities for treatment. Results of the anemia test will be entered into the Household Questionnaire.

## 7.3. Rapid diagnostic tests

Using the same fingerprick made for anemia testing, a drop of blood will be tested immediately using the Paracheck rapid diagnostic test, which tests for *Plasmodium falciparum.* The test includes a loop applicator that comes in a sterile packet. A few microlitres of blood is captured on the applicator and placed on the well of the device. Results are available in 15 minutes. The results will be provided to the respondent in oral and written form and will be recorded on the Household Questionnaire. Those who test positive for malaria will be provided a full course of treatment for malaria according to the national standard malaria treatment guideline in Uganda. They will also be told to go to the nearest health facility immediately if their illness worsens.

## 7.4. Filter paper sample collection

Blood spots will be collected onto prepared filter papers (Whatman no 1, Whatman 3MM; Whatman, Maidstone, UK) in volumes from 1 μl to 45 μl, as per established protocol. Spots will be allowed to dry at ambient temperature and relative humidity overnight and labelled with the individual’s bar codes or ID number on the covering cardboard. Each filter paper will be stored in individual self-sealing plastic bags. These bags will then be transported to a storage facility in boxes with silica gel sachets; each box will be well labelled with the survey details. The blood spots will be used for molecular and immunology studies.

## 7.5. Molecular and immunology studies

DNA will be extracted from filter papers using standard chelex methodology and tested for the presence and speciation of malaria parasites based on nested PCR of cytochrome b (28). Reconstituted filter paper spots will be tested for human malaria-specific IgG antibodies (e.g. anti-MSP-119 anti-AMA-1) by ELISA using standard methodology (29). The prevalence and density of antibody responses will be determined. For antibody prevalence, a cut off above which samples are deemed antibody positive is defined using a mixture model and a pool of malaria naïve European control sera. The sero-conversion rate (SCR or λ) as serological marker of exposure will be estimated by fitting a simple reversible catalytic model to the combined antibody prevalence, stratified into yearly age-groups (29). In the household (community) surveys, the SCR will be determined for each of the three areas separately. The SCR will be related to parasite prevalence and anemia data in the different areas at different time-points. Evidence for changes in transmission intensity will be explored by fitting different forces of infection. In the school surveys a similar approach will be used, estimating an SCR for school-age children. In addition, age-standardized antibody prevalence and density will be calculated.

# STATISTICAL ISSUES

## 8.1 Outcome measures

| Outcome | Definition |
| --- | --- |
| Prevalence of anemia | Proportion of Hb measurements < 11.0 g/dL. Anemia will be classified according to severity: mild (Hb 8.0 – 10.9), moderate (Hb 5.0 – 7.9), severe (Hb < 5.0). |
| Parasite prevalence | Proportion of study participants with a positive thick blood smear at the time of assessment |
| IRS coverage | Proportion of households sprayed |
| ITN coverage. | - Percentage of household with at least one bednet  - Percentage of household with at least one ITN  - Average number of nets per household  - Average number of ITNs per household  - Percentage of children age who slept under any net the prior night  - Percentage of children age who slept under an ITN the prior night  - Percentage of pregnant women who slept under any net the prior night  - Percentage of pregnant women who slept under an ITN the prior night |
| IPT coverage | Percentage of pregnant women on intermittent antimalarial treatment or antimalarial chemoprophylaxis |
| ACT’s coverage | Proportion of febrile episodes in children treated with an ACT |
| Prompt effective treatment of fever | Proportion of children with fever treated within 24 hours of onset of symptoms with an ACT |
| Under five Crude Death Rate (all cause mortality) | The number of children who die by the age of five, per thousand live births. |
| Under five malaria mortality rate | Proportion of deaths in children under five attributed to malaria per thousand live births. |
| Prevalence of malaria specific immune responses | Proportion of study participants with malaria specific immune responses at the time of assessment  Antibody density in participants at the time of assessment |

## 8.2 Analytical plan and sample size/power calculations

Statistical analysis will be undertaken using Stata 10 (Stata Corp., College Station, TX, USA). The prevalence of malaria infection will be based on the thin and thick blood smear readings. This procedure will enable estimation of parasite density, differentiation of Plasmodium species and identification of gametocytes. The proportion of children infected with single and multiple parasite species and the mean intensity of infection/parasite density will be calculated. Differences in proportions by age, sex and transmission setting will be assessed by logistic regression and differences in means using a Student t-test (for parametric data) and a Mann-Whitney test (for non-parametric data). Prevalence of infection and anemia, and coverage rates will be presented as frequencies with appropriate 95% binomial confidence intervals. The report and other related documents will be extensively disseminated to stakeholders. Avenues for dissemination will include publications, working papers, and atlases.

Infection. The primary metric used to measure infection for both the gold standard method (community surveys) and streamlined method (school surveys) will be the parasite rate (PR), defined as the number of positive blood smears divided by the number of smears examined. For the gold standard method, PR will be measured using the cross-sectional surveys of an estimated 300 children (200 households x 1.5 children per household) aged 6-14 years from the community surveys. For the streamlined method, PR will be estimated using cross-sectional surveys of 300 children (3 schools x 100 children per school) aged 6-14 years from the primary school surveys.

We will test the hypothesis that estimates of PR will be similar using the two methodologies. Point estimates of PR will be calculated for each biannual survey and compared using the McNemar’s test of paired proportions. Assuming that we will have a sample size of 300 children per survey for each methodology, we will have 80% power (one-sided significance level of 0.05) to reject the alternative hypothesis that there is a difference in estimates of PR assuming that the absolute difference in PR is no greater than 10% across a range of PRs in the community surveys of 20-80%. Whether or not these analyses show any evidence of significant differences between the methods, we will explore whether there is any systematic bias in the estimate of the streamlined method compared to the gold standard method (e.g. the streamlined method consistently over- or underestimates PR). Ecological logistic regression models will be used to predict the result of the gold standard method using data from the streamlined method, allowing adjustment for bias. Final models will then be prospectively validated in independent test sets to insure their accuracy.

Mortality. The primary metric for malaria mortality will be the relative change in absolute measures of malaria mortality. For the gold standard method, the measure of malaria morality will be the number of malaria-associated deaths in children under 5 years of age per 1,000 live births. Data on malaria mortality using the gold standard method will come from the biannual community surveys and verbal autopsy. For the streamlined method, the measure of malaria morality will be the number of malaria-associated deaths in children under 5 years of age captured by our inpatient surveillance system (described in another protocol).

We will test the hypothesis that relative changes in malaria mortality will be similar using the two methodologies. Point estimates of relative mortality from one year to the next will be calculated and compared, by calculating the variance of the streamlined method using the delta method and the variance of the gold standard method using a bootstrap test. Assuming that we will have a sample size of 800 children per year from the community surveys with baseline mortality rates of 6.5, 12.9, and 19.4 per 1000 (based on 2006 Uganda DHS survey and assuming malaria-attributable mortality of 20%, 40%, and 60%), and baseline number of malaria-associated deaths from our inpatient surveillance of 12, 60, and 84 (based on preliminary inpatient surveillance data) for low, medium, and high transmission sites respectively, we will have 80% power (one-sided significance level of 0.05) to reject the alternative hypothesis that there is an absolute difference in estimates of relative mortality of 1.30, 0.50 and 0.41 for low, medium, and high transmission sites, respectively. Whether or not these analyses show any evidence of significant differences between the methods, we will explore whether there is any systematic bias in the estimate of the streamlined method compared to the gold standard method (e.g. the streamlined method consistently over- or underestimates relative mortality). Log-linear regression models will be used to predict the result of the gold standard method using data from the streamlined method, allowing adjustment for bias.

Immunology. The age-dependent SCR will be determined for each study area at each time-point and related to the concurrent parasite prevalence by RDT, microscopy and PCR and anemia prevalence.

Evidence for a change in transmission intensity will be assessed by fitting more than one force of infection to age-dependent antibody prevalence data. Antibody prevalence and density in school children will be related to the concurrent parasite prevalence by RDT, microscopy and PCR and anemia prevalence.

Decision on the optimal methods for surveillance. If any of the streamlined methods described above do not approximate the corresponding gold standard methods and attempts at correcting systematic bias are not reliable (e.g. unable to consistently predict estimates using the gold standard method) then we will conclude that the streamlined method is not a reasonable substitute for the gold standard method.

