### 5.3.2 Screening of participants

At the end of the household questionnaire, the study personnel will discuss the clinical survey aspect of the study with the head of the household or their designate and adult household members present. Study personnel will briefly describe the purpose of the clinical study in the appropriate language. The inclusion criteria are: 1) Usual residents who are present in the sampled households on the night before the survey, 2) children under 15 years of age or selected household members aged 15 years or older, 3) agreement of parents or guardians of children to provide informed consent, 4) agreement of eligible adults to provide informed consent and 5) agreement of a child aged 8 years or older to provide assent. The exclusion criterion is: 1) inability to locate the child on more than 3 occasions, 2) inability to locate other eligible respondents on more than 3 occasions. All children under 15 years of age will be included for the clinical survey. One person in each of the age category 15-24 years, 25-34 years, 35-44 years, 45-54 years, and > 55 years shall be randomly selected for the clinical survey.

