## 6.0 SCHOOL SURVEYS

## **6.1 Overview.**

Surveys will be conducted in three schools per site which will be randomly selected from a list of all primary schools in the sub-county generated during an enumeration exercise which has already been completed as part of a separate protocol. The surveys will be done twice a year (once during the rainy season and once during the dry season). New lists of three schools will be randomly generated for each survey using replacement; as a result the same school may participate in the survey more than once.

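### School-survey prevalence intervals ignore that each site's 300 children come from only three schools, so they are too narrow and between-site tests too liberal

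*Protocol*

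**What the plan says.** The Study Summary names the prevalence of anemia and of parasitemia as the primary outcome. For its precision, Protocol section 8.2 says "Prevalence of infection and anemia, and coverage rates will be presented as frequencies with appropriate 95% binomial confidence intervals". For comparisons it says "Differences in proportions by age, sex and transmission setting will be assessed by logistic regression".

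The sampling is clustered in both surveys:

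- **Schools.** Section 6.1: "Surveys will be conducted in three schools per site", with "New lists of three schools will be randomly generated for each survey using replacement". Section 8.2 gives the resulting sample as "300 children (3 schools x 100 children per school) aged 6-14 years from the primary school surveys".
- **Households.** Section 5.3.2: "All children under 15 years of age will be included for the clinical survey", plus one randomly chosen member from each older age band. For the age group used in the comparison of methods, section 8.2 counts "an estimated 300 children (200 households x 1.5 children per household) aged 6-14 years from the community surveys".

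The protocol gives no design effect, ICC, cluster-robust variance, random effect or survey procedure for prevalence. The one resampling variance, a bootstrap in section 8.2, is for relative mortality.

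**The concern.** A binomial interval takes every child as a separate, independent piece of information about the sub-county. Children at one school tend to live near each other and share exposure to transmission, so three schools carry less information than 300 independently drawn children. The protocol's own reasoning accepts that schools differ: section 1.3 cites methods for modelling risk between schools, and section 6.6 maps pupils' homes to see where a school's pupils come from.

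The estimated prevalence is the primary result, so its interval is what tells a reader how much a three-school survey can measure. If the interval is too narrow, the streamlined method looks more precise than it is. A logistic regression comparing sites on school data, with no school term, would count chance differences between the sampled schools as differences between transmission settings.

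**Working it through.** **1. The plan's own figure.** Section 8.2 claims 80% power at one-sided 0.05 with 300 children per method and a 10-point difference, for parasite rates (PR) of 20–80%. Taking all children as independent and the true difference as zero:

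power = Φ(0.10 / √[PR(1−PR)(1/n_c + 1/n_s)] − 1.645), where n_c and n_s are the community and school sample sizes.

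At PR 50%: √[0.25 × 2/300] = 0.0408; 0.10/0.0408 = 2.449; Φ(2.449 − 1.645) = 78.9%. At PR 20% or 80% it is 92.2%. The stated 80% is thus matched, to within about a point, at the least favourable PR in the range, with a design effect of 1.

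**2. School clustering.** Inputs: m = 100 children per school and n = 300 (section 8.2). The ICC is not in the protocol and is assumed over a range.

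- Design effect: DEFF = 1 + (m−1) × ICC = 1 + 99 × ICC
- Effective n = 300/DEFF; ratio of true to binomial standard error = √DEFF
- Actual coverage of the nominal 95% interval = 2Φ(1.96/√DEFF) − 1
- Half-width at PR 50% = 1.96 × √(0.25/300) × √DEFF = 5.7 points × √DEFF
- Power as in step 1, with n_c = 300 and n_s = effective n

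| Assumed school ICC | 0.01 | 0.02 | 0.05 | 0.10 |
|---|---|---|---|---|
| DEFF | 1.99 | 2.98 | 5.95 | 10.9 |
| Effective n | 151 | 101 | 50 | 28 |
| True SE / binomial SE | 1.41 | 1.73 | 2.44 | 3.30 |
| Coverage of nominal 95% interval | 84% | 74% | 58% | 45% |
| Half-width at PR 50%, z-based (binomial: 5.7 points) | 8.0 | 9.8 | 13.8 | 18.7 |
| Half-width at PR 50%, t on 2 df | 17.5 | 21.4 | 30.3 | 41.0 |
| Power at PR 50% (stated: 80%) | 64% | 54% | 37% | 26% |

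For two sites compared on school prevalence with the same DEFF, the test statistic is inflated by √DEFF. A nominal two-sided 5% test then rejects with probability 1 minus the coverage above: about 16%, 26%, 42% and 55%.

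**3. Household clustering.** DEFF = 1 + (m−1) × ICC, with household ICC again assumed.

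- m = 1.5 children aged 6–14 (section 8.2), ICC 0.1–0.5: DEFF 1.05–1.25, true SE about 2–12% larger, coverage about 94–92%.
- m = 2.4–3 tested children under 15 (assumed), ICC 0.2–0.4: DEFF from 1 + 1.4 × 0.2 = 1.28 to 1 + 2 × 0.4 = 1.80, true SE 13–34% larger.

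**4. Indicators with the household as unit.** Section 5.1.1 draws households by simple random sampling from a complete enumeration. The proportion sprayed and the proportion owning a net count each household once, so a binomial interval fits.

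**The case against.** Several objections deserve an answer.

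- **Details may sit in a statistical analysis plan.** That would answer silence, but section 8.2 names the binomial interval. The adjective before it does not add a cluster term.
- **The size rests on an ICC that the protocol does not give.** This stands: the figures are illustrations, not estimates of the true error. The direction does not depend on the value, because with 100 children per school even an ICC of 0.01 raises the standard error by 41%.
- **The list of schools in one sub-county is finite.** This would shrink the effect, but the number of schools is not given. If it were 10, the between-school part at ICC 0.05 would be multiplied by 1 − 3/10, giving DEFF = 0.95 + 5 × 0.7 = 4.45 instead of 5.95.
- **Nothing in sampling or data collection is harmed.** This also stands. Sampling is by school, and section 10.3 assigns household identifiers, so the variance can be corrected at analysis.

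A reader might also infer more than the protocol supports:

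- That community intervals are just as bad. At 1.5 children per household the effect is small.
- That all coverage intervals are wrong. Household-unit indicators are not affected.
- That every p-value is too small. Age and sex vary within schools and households, so those contrasts may be little affected.
- That the t-test and Mann-Whitney test are part of the fault. Section 8.2 uses them for means, not prevalence, and does not commit to a three-site comparison of means.
- That false seasonal differences will be declared. Section 8.2 specifies no seasonal test of prevalence.
- That these intervals decide the comparison of methods. Section 8.2 assigns that comparison to McNemar's test, so only its power statement is touched here.

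**Conclusion.** The point holds for school-survey prevalence and for between-site tests on it. Followed as written, section 8.2 gives intervals that are too narrow for any positive school ICC. Over an assumed range of 0.01–0.10 the true standard error is 1.41 to 3.30 times the binomial one, and coverage falls to between about 84% and 45%. The z-based half-widths are lenient, because three schools leave only 2 degrees of freedom. They also take no account of a finite school list or of the equal allocation by class in section 6.4. Household clustering is a secondary, modest effect for children aged 6–14 and somewhat larger when all tested children are analysed. The 80% power statement shares the independence assumption: at PR 50% it is reproduced only with a design effect of 1.

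**What to change.** In section 8.2:

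1. For person-level prevalence, replace the binomial intervals with intervals that treat school (school surveys) and household (community surveys) as clusters. Keep binomial intervals for household-unit indicators.
2. For contrasts between sites, use clustered or mixed logistic regression.
3. Because three schools per site and survey leave 2 degrees of freedom, estimate the between-school variance from one model pooled over all school surveys, rather than separately in each.
4. State an assumed ICC range and restate the power under it. At PR 50%, school clustering alone gives about 64%, 54%, 37% and 26% at ICC 0.01, 0.02, 0.05 and 0.10.

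No new data are needed, and the methods are standard. The price is that reported intervals become wider and the stated power lower. The pooled model in item 3 also assumes that between-school variation is similar across the surveys pooled, which should be said.
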